### Randomization and blinding

Randomization was conducted within the type of surgery using a random number generator, with an equal number of participants in the control and experimental group. An independent researcher had conducted the randomization sequence and the allocation sequence was stored on a secured computer until the participants were assigned to one of the interventions. The medical personnel and trial assessors were blind to the group allocation, but the study participants and research assistant were aware of the allocations. Precaution strategies to prevent the blind from breaking up included a limited number of persons interacting with the patients (i.e. only the research assistant) and a reminder to the patients not to talk about research allocations and study procedure. In addition, the treatment room was a different room of the patient hospital room. In the treatment room patients from the experimental group was exposed to the VR content and psychological respectively physiological measured. For the patients from the control group, only psychological and physiological measures were taken without exposing them to the VR content. After this, each participant was conducted to their hospital room. In the case that a participant explicitly requests to end the study procedure for any reasons, the procedure was stopped and counted as a dropout. Those patients who ask to end the procedure earlier were asked to respond at a short interview to quantify the reasons.

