
## Objectives

The aim of this study is to assess whether exposure to relaxing VR environments is associated with decreased levels of pain after surgery after varicose veins, hernia repair, or gallbladder surgeries. Surgeries of varicose veins, hernia repair, and gallbladder were aggregated due to similarities across (1) the incidence rate [32–34], (2) levels of pain intensity after surgery [35–37], and (3) odds of acute pain to be translated into CPSP [35–37]. We hypothesize that VR-based intervention will have a better result in decreasing pain when it is used as a complementary treatment of standard care compared with the standard care alone. Additionally, we will assess the safety of VR-based intervention in patients after surgery.

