### Study sample size

Using G*Power 3.1.9.2 [39], we had estimated a minimum of 50 participants (25 in each group) needed to detect an effect size of 0.49, with *α* = 0.05 and power = 0.80. The expected effect size of 0.49 was chosen in the light of the results found by the most recent meta-analyses [25, 26], being a conservative effect size given that in their analysis Chan and colleagues [25] found a medium effect size (SMD = − 0.49, 95% CI − 0.83 to − 0.14) and the analysis of Georgescu and colleagues [26] a large effect size was found (Hedges’*g* = 1.08, 95% CI 0.46 to 1.70) for studies with parallel design aiming to decrease pain at hospitalized patients. However, as we expected some dropouts (based on other studies using VR systems for treating anxiety [40]) and some incomplete or unusable data, especially on the physiological measure, we aim to recruit 30 participants in each group.

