#### Inclusion criteria

❖ Adults aged 18–65 years, after surgery of varicose veins, hernia repair, or gallbladder surgery.❖ Patient in the acute care units, 1–3 days following surgery.❖ Willing and able to provide informed consent and participate in the study visit and study follow-up questionnaire.

Presence of any criteria listed below will conduct at the exclusion of the participant from the trial.

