### Outcomes

The present study assesses the efficacy of a Nature Track© VR to decrease pain intensity in surgical patients. The primary outcome is pain intensity measured right before the exposure to the VR content and after. The secondary outcomes measure the effects of the application on relaxation and the amount of time spent by each patient thinking about pain. Also, the primary outcome was complemented with measures of the adverse effects, level of immersion, and level of presence in the VR.

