#### Main analyses

Behavioral data will be analyzed using STATA 16.1 in accordance with the intent to treat principal [56]. Descriptive statistics (i.e., age, gender, assessment of mood, pain catastrophizing, opioid consumption, level of pain intensity, level of relaxation) for the baseline values will be presented within each randomized group. These will include counts and percentages for binary variables and mean and standard deviations, or medians with lower and upper quartiles, for continuous variables, along with minimum and maximum values and missing values. There will be no tests of statistical significance or confidence intervals for differences between randomized groups on any baseline variable. The effectiveness of the intervention on pain intensity (primary outcome) will be assessed by employing random coefficient analysis. We will include the time of assessment, group assignment (VR intervention and standard of care), and the interaction between time of assessment and group in the multi-level regression model. Similarly, for the secondary outcome’s measures (relaxation, time spent by patients thinking about pain, and treatment satisfaction and presence) random coefficient analysis will be performed. Although the intervention is minimally invasive, the adverse effects of the VR intervention will be measured with SSQ scale and pre-post differences will be assessed by *t*-test statistic or the non-parametric equivalent. Physiological data will be processed using the AcqKnowledge 4.1 software, and for each patient, a difference score in the area under the curve between the last 5 min of measurement and baseline level of SC will be extracted. Pearson correlation will be employed to examine the relationship between the level of SC and pain intensity (as a difference score between pre-post intervention). A *P* value will be used to estimate statistical significance for all analyses.

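### Randomisation is stratified by type of surgery but the stated model terms omit it; nothing is biased, but precision is lost if pain change differs between surgery types

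*Protocol article*

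**What the plan says.** Under Randomization and blinding, the protocol article states that "Randomization was conducted within the type of surgery using a random number generator", "with an equal number of participants in the control and experimental group". The Inclusion criteria give three strata: patients "after surgery of varicose veins, hernia repair, or gallbladder surgery". The Objectives explain why the three are studied together: "Surgeries of varicose veins, hernia repair, and gallbladder were aggregated due to similarities across" incidence, pain intensity after surgery and the odds of chronic pain.

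The primary outcome is "pain intensity measured right before the exposure to the VR content and after", so there are two assessments. Under Main analyses, its effectiveness "will be assessed by employing random coefficient analysis", and the terms are named: "We will include the time of assessment, group assignment (VR intervention and standard of care), and the interaction between time of assessment and group". The same method is planned for relaxation and for time spent thinking about pain. Surgery type is not named in the analysis section as a covariate, a model level, a subgroup or a sensitivity analysis.

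**The concern.** When allocation is balanced within strata, differences between strata cancel from the comparison of arms. A model without the stratum does not know this. It counts those differences as noise and reports a standard error larger than the real one. Confidence intervals are then too wide and the test rejects too seldom. A trial aiming for 30 patients per arm has little power to spare.

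The article names its model terms, so this is a stated model that does not follow the stated randomisation, rather than a detail left unsaid.

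**Working it through.** The plan gives no figure for differences between surgery types, so there is none to reproduce.

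**Inputs from the article:** three surgery types, 1:1 allocation within each, two pain assessments, terms time, group and time by group, a target of 30 per arm, and a standardised effect of 0.49.

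**Assumptions:** exactly equal arms within each type, both assessments available for every patient, and a patient-level random intercept. R² is the share of the variance in pain *change* explained by surgery type, set at 5%, 10% or 20%.

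**Step 1: what time by group estimates.** With two assessments it is the mean pre-post change in the VR arm minus that in the control arm. A surgery effect that is the same before and after is subtracted out of each patient's change. Four trials of 60 were simulated with surgery types shifted by -1, 0 and +1 points at both assessments, and models with and without a surgery main effect were fitted. The time-by-group result was identical in each trial, for example -0.6867 (SE 0.3837) both ways. A main effect alone therefore does nothing for this term.

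**Step 2: when change differs by surgery type.** Let V be the total within-arm variance of change, with n per arm.

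- SE² reported without surgery type: 2V/n
- True SE² under balance within types: 2V(1 - R²)/n
- Ratio of SEs: 1/√(1 - R²)
- Actual size of a nominal 5% test: 2[1 - Φ(1.96/√(1 - R²))]

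| R² of change | SE ratio | SE overstated by | Actual test size |
|---|---|---|---|
| 5% | 1/√0.95 = 1.026 | 2.6% | 0.044 |
| 10% | 1/√0.90 = 1.054 | 5.4% | 0.039 |
| 20% | 1/√0.80 = 1.118 | 11.8% | 0.028 |

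**Step 3: simulation at 30 per arm.** Three types of 20 patients were used, with arms balanced in each, an assumed pre-post correlation of 0.6 and 4,000 runs per cell. The effect is 0.49, in units of the within-type SD at one assessment. Change was regressed on group, without and with surgery type; the latter corresponds to surgery type by time in the longitudinal model. Monte Carlo error is about √(0.05 × 0.95/4000) = 0.003 for type I error and √(0.5 × 0.5/4000) = 0.008 for power.

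| R² of change | Type I error, omitted | Type I error, included | Power, omitted | Power, included |
|---|---|---|---|---|
| 0% | 0.046 | 0.045 | 0.56 | 0.56 |
| 10% | 0.043 | 0.054 | 0.49 | 0.53 |
| 24% | 0.024 | 0.051 | 0.43 | 0.55 |
| 44% | 0.006 | 0.048 | 0.28 | 0.54 |

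The power columns compare the two models only. They do not re-assess the sample size, because they rest on the assumed correlation. The last two rows lie beyond the range used in Step 2 and show direction.

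**Step 4: what inclusion costs.** Residual degrees of freedom for change fall from 58 to 56. If the types show no difference at all in observed change, the SE rises by at most √(58/56) = 1.018. In the four trials of Step 1, which had no surgery effect on change, it rose from 0.3837 to 0.3887, 0.3658 to 0.3719, 0.3442 to 0.3464 and 0.3773 to 0.3789, that is by 0.4% to 1.7%.

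**Step 5: the outcome measured once.** Time spent thinking about pain is recorded only after the session. Nothing is subtracted out, so differences in level between surgery types do enter the error. The Step 2 formula applies, with R² as the share of variance in that score.

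**The case against.** The strongest objection concerns the mechanism. A reader might infer that any difference in pain level between surgery types inflates the primary standard error, and that a surgery main effect would cure it. Step 1 shows neither is so for the stated model: stable differences cancel. This stands, and it makes the loss conditional on differences in *change* over one short session.

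The Objectives also point to similar pain intensity after the three operations, which suggests that stratum effects may be small. That stands as a reason for modest expectations. It does not remove the point: the passage justifies pooling, does not say the factor will be left out of the analysis, and does not speak of change in pain.

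The article says which terms will be included, not that no others will be, and an analysis plan not shown could add surgery type. This is fair. However, no other term is named anywhere, and adding one would alter the model as published.

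Finally, one might extend the point to simulator sickness and skin conductance. Main analyses does not support that. Simulator sickness gets a pre-post comparison, and the skin conductance difference score is correlated with pain change. Neither has a stated between-group model.

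**Conclusion.** The stated model terms omit the factor used to stratify the randomisation. A reader might take this as a threat to validity, but the document does not support that reading. Allocation within strata leaves the treatment estimate unbiased, and the error is towards too few rejections, not too many.

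What remains is a conditional loss of precision. The standard error of time by group is overstated by about 2.6% to 11.8% if surgery type explains 5% to 20% of the variance in pain change. There is no material difference if it explains none. The range is assumed, and the figures require equal arms within each surgery type and complete pairs of assessments. Severity is low to moderate, and the correction is a free improvement.

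**What to change.** - **Pain and relaxation:** add surgery type and surgery type by time to the random coefficient model. Alternatively, analyse the post score adjusted for the baseline score and surgery type. A surgery main effect alone is not enough.
- **Time spent thinking about pain:** add surgery type as a three-level fixed effect.
- **Simulator sickness and skin conductance:** no change on this account.

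The cost is about 2 degrees of freedom out of 58 and a line in each model statement. Surgery type is known for every patient because it determines eligibility and allocation. The Trial status section reports that the data had not yet been analysed, so the choice can be fixed in writing before results are seen. That also avoids a later choice between adjusted and unadjusted results.

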### Recruitment procedure and interventions

The recruitment process and data collection are presented in Fig. 1. No specific strategy for improving adherence was planned. The day following the surgical procedure, all patients from the acute care unit who meet the primary criteria for inclusion (i.e., age, type of surgery, type of opioids used, free of visual impairments, able to fluently speak in Romanian and without recorded psychological problems) were invited to participate. Information regarding duration, procedure, implications, and conditions for withdrawing were presented and explained. To the interested patients, the research assistant presented the informed consent asking to read and sign as a final statement regarding their decision to enroll in the study. Subsequently, those who have signed the informed consent were invited to the treatment room where they have completed the Six-item Cognitive Impairment Test for assessing the eligibility regarding executive functions. Finally, those patients with intact executive functions were randomly allocated to one of the two groups:

**Fig. 1 Fig1:**
[figure not shown]
Flowchart of the study based on the Consolidated Standards for Reporting of Trials

#### Treatment group: VR-based intervention

Patients allocated to the VR-based intervention followed the standard protocol after surgery as prescribed by the current medical personnel and exposed for 15 min to an interactive virtual environment (i.e., Nature Treks© VR). This application is a commercially available app from the Oculus store (available at https://www.oculus.com/experiences/go/1723271804396968/), promoting relaxation through fifteen highly immersive environments. Each environment recreates a different natural scene (e.g., a tropical beach, savannas at sunset, snowy forests) which can be explored by the patients through a controller. Concomitant with the activities (e.g., walking on the beach, climbing the mountains) environmental effects are changing smoothly to create a vivid experience. Additionally, in some environments (i.e., deep blue and black beginning), patients can freely explore the scenes in 360 degrees for enhancing the feeling of presence and immersion.

As previous studies testing the efficacy of the analgesic effect of VR [30] showed that better immersion is associated with lower scores for pain intensity, the device used is an Oculus Rift® (available at - https://www.oculus.com/). This device is the premium device from Oculus, equipped with a highly immersive headset, one controller, and integrated headphones.

Five minutes before and during the VR exposures, the fluctuations of skin conductance (SC) were measured for all patients. Before and after the intervention, pain intensity, relaxation, and VR adverse effects were assessed. Additionally, the catastrophizing level, anxiety, and depression related to health and presence in the VR environment were quantified.

#### Control group: standard of care intervention

Patients allocated to the standard of care group followed the treatment after surgery as prescribed by current medical personnel. In addition, they followed the same protocol as the patients in the intervention group regarding psychological and physiological measures. Specifically, they were conducted in the treatment room and asked to indicate the non-dominant hand for setting up the equipment to SC measures. After that, the SC was measured continuously for 20 min without exposure to the VR environments. At the end, they completed de psychological measures and were conducted in their hospital room.

### Data collection procedure

Figure 2 offers an overview of the process of the data collection and measures. There is no anticipated harm and compensation for trial participation. This trial does not involve collecting biological specimens for storage. All psychological and physiological measures were collected by a previously trained researcher which had weekly meetings with RG and HS to discuss the potential difficulties and assess the adherence to the study protocol. The level of pain intensity and relaxation was collected before and after the exposure to VR environments in the experimental group, respectively before and after physiological measures in the control group. The SC was measured during the exposure to VR content in the experimental group and for a period of 15 min in the control group. For ensuring an accurate baseline for the physiological measure and for controlling the individual differences in SC, the signal of SC for each participant was taken before the study procedure start for 5 min. During this time, participants had no other instructions, and the communication was maintained at the minimum level. The amount of analgesic consumption for each participant will be extracted from the medical records. Excepting for the fluctuations of skin conductance, all measures were collected through an online platform.

**Fig. 2 Fig2:**
[figure not shown]
Overview of the enrollment, intervention, and assessment measures

### Outcomes

The present study assesses the efficacy of a Nature Track© VR to decrease pain intensity in surgical patients. The primary outcome is pain intensity measured right before the exposure to the VR content and after. The secondary outcomes measure the effects of the application on relaxation and the amount of time spent by each patient thinking about pain. Also, the primary outcome was complemented with measures of the adverse effects, level of immersion, and level of presence in the VR.

## Measures

### Primary measures

#### Pain

The pain intensity was measured using the Numerical Rating Scale (NRS) [41] by asking participants to report their intensity before and after the intervention on a scale from 0 (“no pain”) to 10 (“extremely painful”). To help patients to discriminate between different pain levels, they were asked to report the mean level of pain intensity in the last 24 h, the peak of intensity in the same period, and the intensity right before the intervention. We chose NRS for this study rather than other measures more extensively used, such as visual analog scales (VAS), due to the consensus of the better psychometrics properties [42–45]. The value of pain right before the intervention will be used in the analysis of VR effectiveness.

Concomitantly, as a physiological indicator of postoperative pain were measured the fluctuations of the SC [46–48]. The SC were measured using the BIOPAC MP150 system (Biopac Systems, CA,USA). The two finger electrodes were attached to the first phalange of the index and medius fingers from the non-dominant hand with Velcro straps. The electrodes were connected to the computer using the USB connection input. To ensure good contact with the skin, isotonic gel was added to the electrodes prior to attaching to the fingers. At the beginning, participants had few minutes to relax, get ready and comfortable with the experimental environment. After that, patients were instructed not to move for the duration of the recording.

### Secondary measures

#### Relaxation

As the level of relaxation could affect the perception of the pain intensity, the state of relaxation was measured using the NRS from 0 (“extremely stressed” to 10 (“relaxed”) before and after the intervention. We chose to measure by using NRS rather than other scales designed to measure relaxation due to his factual effect and similarities with the pain intensity measures.

#### Time spent thinking about pain

Another factor which can contribute to an increased perception of pain intensity is the amount of thinking time spent by a patient at pain [49]. Consequently, we asked patients to report after the interventions, on NRS from 0 (“not at all”) to 10 (“all the time”), the amount of time they spent thinking about their pain during the exposure to the VR content in the experimental group and during the measuring of SC conductance in the control group.

#### Adverse effects

Potential adverse effects were evaluated using the Simulator Sickness Questionnaire (SSQ) [50]. As some of the unintended effects of VR could also be effects of the opioid’s consumptions (e.g., headaches, nausea), we have asked participants to complete the scale twice, before and after the exposure of VR. The SSQ was previously validated and proved robust psychometric properties [50, 51] being the most widely measure of cyber-sickness. The patients were instructed to answer on a 4-point Likert scale, corresponding to not at all, slight, moderate, and strong sensations regarding the occurrence of possible side effects such as general discomfort, fatigue, headache, and dizziness.

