By using a combination of technologies (i.e., head-mounted display-HMD, vibro-tactile gloves, individualized sounds, and gesture-sensing joysticks), VR environments create immersive [21] and multi-sensorial experiences [22]. Immersion in the virtual world is believed to facilitates the shifting of attention away from the painful stimuli or from the experience of pain, to more engaging or enjoyable stimuli, developing effective distraction strategies and reshaping the pain perception [23, 24]. A recent meta-analysis [25] estimating the efficacy of VR interventions for acute pain management in clinical settings found a medium effect size of these interventions (standard mean differences (SMD) *=* − 0.49, 95% CI − 0.83 to − 0.14). Moreover, a subsequent meta-analysis [26] relying only on randomized controlled trials (RCT) conducted in hospital settings showed significant effects of VR-based interventions to reduce pain intensity during medical procedures (7 studies, Hedges’*g* = 1.09, 95% CI 0.25 to 1.92) and after the medical procedures (12 studies, Hedges’*g* = 1.08, 95% CI 0.46 to 1.70). Moreover, comparable results were founded when interventions aimed to reduce the cognitive (8 studies, Hedges’*g* = 0.82, 95% CI 0.39 to 1.26) or affective components of pain (14 studies, Hedges’*g* = 0.55, 95% CI 0.34 to 0.77). However, these promising results of VR interventions integrated into acute pain management are hampered by the fact that none of the analyses includes studies on post-surgical patients. In spite that the VR technology could be effectively exported in medical care settings [25] as a potentially cost-effective tool [27], to date, in postoperative care, only a few studies examined its efficacy. In this sense, the pain literature discusses the findings of Mosso-Vazquez and colleagues [28] which showed that 30 min of VR exposure can reduce pain intensity after cardiac surgery regardless if the pain relief was self-reported or assessed through physiological measurements (i.e., breathing rate, arterial pressure, and heart rate). Similarly, a subsequent study of Mosso-Vazquez and colleagues [29] comparing two different VR devices (i.e., HMD and mobile VR) for pain relief during ambulatory surgery revealed that both technologies decreased pain intensity, with better results for VR environments delivered through HMD. This result is consistent with other results proving that high-quality VR environments create a better distractor from pain [30] although the estimates were not in postoperative settings. Nevertheless, while these studies conducted by the Mosso-Vazquez and colleagues [28, 29] had positive and clinically significant results, highlighting the potential usefulness of VR in postoperative pain management, these studies were uncontrolled and possibly accompanied by overestimations of the VR efficacy. As far as we know, to date, there are no studies estimating the effectiveness of VR for postoperative pain following surgery under general anesthesia in a randomized clinical manner. In addition, the VR contents used in previous studies were intended only to distract patients from pain. Using environments that promote relaxation stimuli rather than distraction stimuli can be particularly useful because a relaxed state of mind was associated with a reduced demand of tissue oxygen and a reduced level of lactic acid, both being harbingers of a decreased level of pain [31]. In addition, relaxation was associated with an increased level of endorphins, lower levels of anxiety, and skeletal muscle tension. As such, the present protocol proposes a randomized controlled trial, to assess the effectiveness of relaxing VR environments for pain relief at patients in the first days after surgery.

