## Discussion

Treating pain after surgical interventions is an overly complex and challenging process (61,62), and the integration of non-pharmacological approaches has been one of the priorities of healthcare reform in the last years [5]. Additional interventions along the standard pharmacological treatments are strongly recommended by the guidelines for postoperative pain management [5]. Limited medical personnel resources and short periods of hospitalization are widely known problems of the postoperative management, highlighting the need for additional interventions that are requiring very little set-up time to co-occur with the standard pharmacological treatment. Addressing these problems, VR interventions can be used as a non-pharmacological tool for reducing pain after surgery. The present protocol offers a detailed description of a randomized and controlled clinical trial to determine the effectiveness of VR environments in reducing pain intensity in surgical patients.

Should the hypotheses suggested in this study be proven, this would add empirical evidence about the benefits and feasibility of VR for the pain treatment in surgical patients. Our expectation is to obtain greater pain relief compared with studies employing non-technological interventions. Moreover, we expect that the results of the present study to be in line with the ones conducted by Mosso-Vazquez and colleagues [32] as well with studies that use VR for non-surgical patients [29, 30]. In addition, we expect to find minimal side effects in those patients exposed to VR and the level of willingness to use VR sessions in the future treatment of pain to be high.

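### The only stated harm analysis is a group-level test of pre-post SSQ change, which in about 30 VR patients is insensitive to marked sickness in a few; individual worsening should be reported beside it

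*Protocol article*

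**What the plan says.** The Objectives section makes safety a declared aim: "Additionally, we will assess the safety of VR-based intervention in patients after surgery".

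The Adverse effects section uses the SSQ, completed before and after VR exposure. Answers are on a "4-point Likert scale, corresponding to not at all, slight, moderate, and strong sensations", and the symptoms named are "possible side effects such as general discomfort, fatigue, headache, and dizziness". The reason given for the first measurement is that headache and nausea may also come from opioids.

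The Main analyses section fixes the analysis: "the adverse effects of the VR intervention will be measured with SSQ scale and pre-post differences will be assessed by" a t-test or its non-parametric equivalent. It does not say whether the total score, subscales or single items are tested.

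The Discussion states the expected result: "we expect to find minimal side effects in those patients exposed to VR".

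One other source of tolerability information exists. Under Randomization and blinding, a patient who asks to stop is counted as a dropout and interviewed briefly about the reasons. The Study sample size section plans 30 patients per group.

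**The concern.** A pre-post test asks whether the group as a whole has shifted. Safety of a single VR session is mainly a question about individuals: how many became clearly nauseated or dizzy. If most patients do not change and a few react strongly, the mean moves little. The reactors also inflate the SD in the denominator of the test statistic. A rank test does not help, because it looks for a shift in the typical patient.

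The SSQ also places general complaints (discomfort, fatigue, headache) beside VR-type symptoms such as dizziness. Patients 1 to 3 days after surgery may already have the general complaints before the session. If some of these ease during a relaxing session, falls in many patients could offset rises in a few.

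At stake is the safety conclusion. The article expects few side effects and plans no interim analysis, stopping rule or data monitoring committee. The SSQ result is thus the main evidence on harm, and a non-significant test could be taken as support for that expectation.

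**Working it through.** The article gives no SSQ sickness rate, SD, relevant change or power, so there is no stated figure to reproduce. The question is how often the stated test would show harm if a few patients clearly worsened.

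**Inputs**
- n = 30 VR patients (Study sample size).
- Test: one-sample t-test on the pre-post change, two-sided 5% level (assumed), critical value 2.045 on 29 df.
- Assumed: k = 3 or 5 patients worsen by w = 6 or 10 raw points (6 points is, for example, three items going from not at all to moderate). All patients vary at random with SD 2 or 3. The other n − k patients improve by r = 0, 0.5 or 1 point on average.

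**Hand check, k = 5, w = 6, r = 0**
- Mean change = 5 × 6 / 30 = 1.0.
- Variance added by the reactors = [k(n − k)/n] × w² / (n − 1) = (5 × 25/30) × 36 / 29 = 5.17.
- With SD 2: total SD = √(4 + 5.17) = 3.03; SE = 3.03/√30 = 0.553; t ≈ 1.0/0.553 = 1.81.
- With SD 3: total SD = √(9 + 5.17) = 3.76; SE = 0.687; t ≈ 1.46.

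Both typical t values lie below 2.045, so the test misses the harm more often than it finds it.

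**Simulated chance of significant worsening (t-test, SD 2)**

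| Reactors | r = 0 | r = 0.5 | r = 1 |
|---|---|---|---|
| 3 at +6 | 14.8% | 1.0% | about 0% |
| 5 at +6 | 37.7% | 6.0% | 0.4% |
| 5 at +10 | 57.6% | 14.5% | 1.2% |

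With SD 3, 5 at +6 and no relief, the chance is about 25%. The range for that scenario is therefore about 25% to 38%. The signed-rank test does no better: 25.8%, 2.2% and 0% for 5 at +6 with SD 2.

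**Relief that cancels the harm exactly**

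The mean change is zero when r = k × w / (n − k):
- 3 at +6: 18/27 = 0.67 point.
- 5 at +6: 30/25 = 1.20 points.
- 5 at +10: 50/25 = 2.00 points.

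**What a patient count would show**
- With a true reaction rate of 10%, the chance of at least one case in 30 is 1 − 0.9³⁰ = 95.8%.
- 3/30 = 10% (exact 95% CI 2.1% to 26.5%); 5/30 = 16.7% (5.6% to 34.7%).
- 0/30: upper limit = 1 − 0.025^(1/30) = 11.6%.

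**The case against.** A reader might infer that the SSQ contains symptoms the VR session is meant to relieve, so that relief will hide sickness and VR will look free of side effects. The article does not support this. Its targets are pain, relaxation and time spent thinking about pain; the Background describes the purpose as "to assess the effectiveness of relaxing VR environments for pain relief at patients in the first days after surgery". Fatigue and headache are never named as targets, and headache and nausea are linked to opioids. Relief of general discomfort is a reasonable inference, but no more. This objection stands, so relief is treated here only as a possible aggravation. The core point does not need it: the r = 0 column has no relief in it.

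Four further objections stand in part.
- The article does not state the score level tested, so pooling of dizziness with fatigue cannot be asserted. Scoring and tabulation detail may properly sit in a fuller document. The choice of a group-level test, however, is stated.
- Severe reactions are not wholly invisible, because early stoppers are asked why. That misses patients who finish the session with symptoms.
- No rule infers safety from a non-significant test. The expectation of few side effects is a Discussion remark, so false reassurance is a risk and not a certainty.
- The sizes rest on assumed inputs. Excluding patients with a history of motion sickness may lower the reaction rate. With 5 patients at +10 points, SD 2 and no relief, the test finds harm in more than half of trials.

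**Conclusion.** The point holds in a limited form. For a declared safety aim, the article fixes one harm analysis, and that analysis is insensitive to marked worsening in a few patients. With 5 of 30 worsening by 6 raw points and an SD of change of 2 to 3, it shows significant worsening in about 25% to 38% of trials; with 3 such patients and SD 2, in about 15%. Relief on general items in the other patients would lower these figures sharply, but that is conjecture. All sizes depend on assumed reaction rates, SDs and relief.

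The documents do not establish that VR will appear harmless, or that the test will necessarily pool general and VR-type symptoms. They do leave room for a non-significant result to be taken as confirming few side effects. The primary outcome is not affected.

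**What to change.** Keep the planned test and add a patient-level safety result to the Main analyses section:

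1. For the VR arm, report the number and percentage of patients with any SSQ item newly rising to moderate or strong after the session. Show this by item or subscale, so that nausea and dizziness can be seen separately from discomfort, fatigue and headache.
2. Add the number who stopped early because of symptoms, from the interviews already described.
3. Give exact 95% confidence intervals, including the upper limit when no event is seen (11.6% for 0/30).
4. Add the control-arm count and a risk difference only if controls completed the SSQ both before and after. The Control group section says they followed the same protocol for psychological measures, but a pre-session SSQ in controls is not stated outright.
5. State that safety will not be concluded from a non-significant group test.

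For the VR arm this needs no new data: it uses SSQ answers and stopping reasons already collected. Recruitment has ended, so a missing control measurement could not be added. The Trial status section says the data had not been analysed at that version, so the addition could then still be specified in advance. There are two costs. The safety statement becomes less favourable, because the upper limit stays above 10% even with no events. The moderate-or-strong cut-off is a convention, and it has to be fixed before analysis.
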